**Fig. 2 Fig2:**
[figure not shown]
Schedule of enrollment, interventions, and assessments of the study. MRI (T1, RS-fMRI, DTI), magnetic resonance imaging (high-resolution anatomical, resting-state functional MRI, diffusion tensor imaging)

### Participants

The inclusion criteria are as follows: to be eligible, subjects must (1) be over 30 but less than 85 years old; (2) have had their first stroke within the past month; (3) have a diagnosis of acute stroke confirmed by a neuroimaging neurological assessment (computed tomography or MRI); (4) have a starting upper-limb function of Brunnstrom [37] stage II~IV; and (5) have good cognitive ability (Mini-Mental State Examination (MMSE) [38] cutoff > 23).

The exclusion criteria are as follows: (1) history of transient ischemic attack (TIA); (2) failure of critical organs, such as heart, lung, liver, and kidney; (3) previous history of brain neurosurgery or epilepsy; (4) severe cognitive impairments or aphasia (incapable of understanding the instructions given by therapists); (5) not suitable for an MRI scan (including but not limited to: metal fragments in eyes or face; implantation of any electronic devices such as (but not limited to) cardiac pacemakers, cardiac defibrillators, cochlea implants or nerve stimulators; surgery on the blood vessels of brain or the valves of the heart; claustrophobia; or brain or skull abnormalities); (6) life expectancy < 3 months; and (7) enrollment in another clinical trial involving physical therapy or an investigational drug.

### Sample size considerations

This randomized controlled trial is a two-group independent design examining the effects of immersive VR on rehabilitation of subjects with subacute stroke. We assumed a two-tailed comparison and set the type I error rate at 0.05 with 80% power. We plan to screen approximately 100 individuals with subacute stroke. After screening, 80 subjects will be recruited and randomized to the experimental group or the control group. As a conservative estimate (dropout rate = 25%), we presume that 60 subjects will complete the study. To reduce the dropout rate, we will employ two strategies to keep participants engaged: regular communication via phone or social media and clinician visits. After conducting a power analysis based on the aforementioned statistical parameters using the software GPower3.1.9.2 [39], the effect size is calculated as 0.74, which is between a medium (0.5) and large (0.8) effect size [40]. Moreover, there is evidence from a small sample (8 subjects) that VR-enhanced treadmill training for 5 sessions per week over 3 weeks induces significant cerebral reorganization [41]. Thus, 30 subjects for one group is sufficient to assess the effectiveness of immersive VR training in post-stroke rehabilitation in eliciting upper-limb motor recovery post-stroke compared to traditional rehabilitation training, and to investigate the underlying brain mechanisms of immersive VR-based rehabilitation using three MRI modalities.

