**Methods:**

Subjects (*n* = 60) with subacute stroke (defined as more than 1 week and less than 12 weeks after stroke onset) will be recruited to participate in a single-blinded, randomized controlled trial. Subjects will be randomized 1:1 to either (1) an experimental intervention group, or (2) a conventional group (control). Over a 3-week time period immediately following baseline assessments and randomization, subjects in the experimental group will receive both immersive VR and conventional rehabilitation, while those in the control group will receive conventional rehabilitation only. During the rehabilitation period and over the following 12 weeks, upper extremity function, cognitive function, mental status, and daily living activity performance will be evaluated in the form of questionnaires. To trace brain reorganization in which upper extremity functions previously performed by ischemic-related brain areas are assumed by other brain areas, subjects will have brain scans immediately following enrollment but before randomization, immediately following the conclusion of rehabilitation, and 12 weeks after rehabilitation has concluded.

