### Study design

The Institutional Review Board of the Second Affiliated Hospital and Yuying’s Children Hospital, Wenzhou Medical University, China, approved this study. Prior to inclusion, all subjects will be informed about the objectives and procedures of the study. Subjects who meet the inclusion criteria must provide informed consent before entering into the study.

Subjects (*n* = 60) diagnosed with stoke in its subacute stage (defined as more than 1 week and less than 12 weeks after stroke onset) from an in-patient stroke rehabilitation unit in China will be enrolled in a single-blinded randomized controlled trial for 15 weeks. They will be randomized in a 1:1 fashion into (1) a new 3-week rehabilitation training program with an immersive VR system, (2) a 3-week conventional rehabilitation program. The random allocation will follow a covariate-adaptive randomization procedure [34, 35]. Each subject will be randomly assigned a code based on computer-generated, stratified, permuted block randomization with a block size of 8 and balanced by age and location of stroke.

All subjects will receive three assessments at the following time points: immediately following enrollment but before randomization (week 0), immediately following conclusion of the randomized rehabilitation program (week 3) and follow up 12 weeks after conclusion of the rehabilitation program (week 15). The assessment includes inclusion and exclusion of subjects, clinician-filled questionnaires and MRI scans. To avoid assessment bias, all inclusion and exclusion assessments and clinician-filled questionnaires will be completed by physiotherapists who are blinded to this study and with at least 2-years of experience in physical therapy. The flow chart for the study is shown in Fig. 1 and the schedule of enrollment, interventions, and assessments of the study (as recommended by Standard protocol items: recommendation for interventional trials (spirit) 2013 [36]) is shown in Fig. 2.

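### The article gives 60 as the number randomised in two places and 80 in a third; the stated 80% power holds for 80, and for 60 only if nobody drops out

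*Protocol article*

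**What the plan says.** Three places in the protocol article give a size for the trial.

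- Abstract, Methods: "Subjects (*n* = 60) with subacute stroke" are to be recruited, and the same subjects are then randomised 1:1.
- Study design: "Subjects (*n* = 60) diagnosed with stoke in its subacute stage" are to be enrolled, and they are then randomised 1:1.
- Sample size considerations: "After screening, 80 subjects will be recruited and randomized to the experimental group or the control group". The next step is "As a conservative estimate (dropout rate = 25%), we presume that 60 subjects will complete the study".

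The power statement stands in the last of these sections. The design is two independent groups, and the error rates are given as "We assumed a two-tailed comparison and set the type I error rate at 0.05 with 80% power". From these, "the effect size is calculated as 0.74, which is between a medium (0.5) and large (0.8) effect size". The section concludes that "Thus, 30 subjects for one group is sufficient to assess the effectiveness of immersive VR training in post-stroke rehabilitation".

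The Statistical analysis section adds that an intention-to-treat analysis will be done if subjects are lost, with missing values for all enrolled subjects filled by carrying the baseline observation forward.

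**The concern.** Sixty and 80 cannot both be the number randomised. The number 60 can be traced: it is the expected count of completers. The abstract and the study-design section, however, use it for subjects who enter the trial and are then allocated, so it cannot be read there as completers.

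The difference matters because the power statement rests on 30 completers per arm. The allowance for dropout exists only if 80 are randomised. If recruitment, which the article reports as underway, stops at 60, that allowance is gone, and any dropout takes the trial below the power it claims. A null result could then be read as coming from a trial with 80% power at 0.74 when it did not have it.

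**Working it through.** **Inputs.** Two-sided alpha 0.05, power 80%, two independent groups, 30 per group, 25% dropout and d = 0.74 (all Sample size considerations). Number randomised: 80 (same section) or 60 (Abstract; Study design). Allocation 1:1 (Study design).

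**Method.** Two-sample t test. Power = P(|T| > t_crit), where T is noncentral t with n1 + n2 − 2 degrees of freedom and noncentrality d × √(n1·n2/(n1 + n2)).

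**Step 1: reproduce the stated figures.**
- Inflation for dropout: 60/(1 − 0.25) = 80, and 80 × 0.75 = 60. Correct.
- With 30 per arm, the d that gives 80% power is 0.736, which rounds to 0.74. Reproduced.
- Power at d = 0.74 with 30 per arm: noncentrality 0.74 × √15 = 2.866, power 80.5%. The smallest n per arm that reaches 80% is 30 (29 per arm gives 79.1%).

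So the section is internally correct for 80 randomised and 60 completing.

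**Step 2: 60 randomised, 25% dropout, completers analysed.**
- 60 × 0.75 = 45 completers, split 22/23.
- Noncentrality 0.74 × √(22 × 23/45) = 2.481, power 67.9%, about 12 points below 80%.
- Detectable d at 80% power: 0.855.

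**Step 3: how far this depends on dropout** (60 randomised, completers analysed, d = 0.74).

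| Dropout | Completers | Power |
|---|---|---|
| 0% | 60 | 80.5% |
| 5% | 57 | 78% |
| 10% | 54 | 76% |
| 15% | 51 | 74% |
| 25% | 45 | 68% |

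**Step 4: 60 randomised, all analysed with baseline carried forward.** The nominal n stays at 30 per arm, but a dropout enters with zero change.
- Assume 25% drop out in each arm, the effect in completers is 0.74, and the SD is unchanged. The effect becomes 0.74 × 0.75 = 0.555, and power with 30 per arm is about 56%.
- If the SD is recomputed to allow for the mixture, the answer depends on the mean control-arm change, which the article does not give. For an assumed 0 to 2 SD, power runs from about 66% down to 35%.
- Under the first of these assumptions, 80 randomised (40 per arm) gives about 69%. This dilution is therefore not peculiar to 60; it shows that the stated 80% describes a completers comparison.

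**The case against.** The best defence is that the sample-size section contains no arithmetic error. It is the detailed statement, it shows where 60 comes from, and the likeliest repair is a wording change in the abstract and the study-design section. That stands. The fault is an internal inconsistency, not a miscalculation.

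A reader might infer that randomising 60 in itself forfeits the power. The article does not support that: with no dropout, 60 randomised gives 80.5%. The loss needs dropout as well. The 25% is described as conservative and is accompanied by retention measures, so the true loss could be smaller, as the table in the working shows. It is nevertheless the rate the plan chose to design for.

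A second fair objection is that 68% is a completers figure, whereas the plan analyses all enrolled subjects. That also stands, and 68% should not be written in as the power of the planned analysis. It does not rescue the 80%, because carrying baseline forward shrinks the difference.

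A reader might also infer that any sample size would pass as sufficient by the article's reasoning, since 0.74 is solved from n. That goes too far. The text sets the result against medium and large benchmarks, and a sufficiently small sample would exceed the upper one. Solving for a detectable effect is legitimate, provided it is labelled as such. Nor is the finding cited in the Background, that non-immersive VR was not significantly better than conventional therapy, evidence on the immersive effect; the article attributes it to a lack of relevant tasks.

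The Discussion does name the limited sample size as a limitation, but that does not settle which number is meant. The study flow chart is not in the text at hand, so whether it gives a number randomised could not be checked.

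**Conclusion.** The inconsistency is real and must be corrected: a core design figure is stated twice as 60 and once as 80. The stated power and detectable effect hold for 80 randomised with 60 completing, or for 60 randomised with no dropout. For 60 randomised with 25% dropout, a completers analysis has about 68% power at d = 0.74, with a detectable d of about 0.85. These figures assume a two-sample t test and a near-even split of the 45 completers. The figure of about 56% under baseline carried forward rests on the further assumptions of zero change in dropouts, equal dropout in both arms and an unchanged SD.

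A lesser point is that 0.74 is solved from 30 per arm, alpha and power. It is what 60 completers can detect, not an effect the article expects or justifies. This is a matter of labelling and does not carry the weight of the enrolment conflict.

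**What to change.** State one number randomised in the abstract, the study-design section and the sample-size section, and keep it distinct from the number expected to complete.

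- If 80 is right: say in the abstract and the study-design section that 80 are randomised and 60 are expected to complete. The sample-size figures can stay.
- If 60 is right: restate the power or the detectable effect in the sample-size section for 60 randomised with 25% dropout, and name the analysis set it refers to (completers, or all enrolled with baseline carried forward).

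In either case, call 0.74 the minimum detectable standardised effect at 80% power for 60 completers.

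The cost is a text correction. No subjects are needed beyond the 80 already in the sample-size section. The downside is that, if 60 is the true number, the restated power may be less favourable than the one now printed.

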### Intervention design

Subjects in the control group will receive 60-min conventional rehabilitation training per day, 5 days per week for 3 weeks. This conventional rehabilitation delivered by a therapist at the hospital includes physical and occupational therapy (upper extremities flexion and extension training) which comprise task-related practice for gross movements and dexterity, including different grips and selective finger movements, strength training, stretching, and training in daily life activities. Conventional rehabilitation will be designed with similar intensity and complexity to simulate the skills required in the immersive VR group. Researchers in the study will supervise and encourage all participant to fully participate in the training to guarantee the quality of the training. In contrast, subjects in the experimental group will receive 30 min of conventional rehabilitation and 30 min of immersive VR rehabilitation training per day, 5 days per week for 3 weeks conducted by a therapist at the hospital. The details will be discussed in the section “VR training protocol”.

### VR system

Shown in Fig. 3a, the VR system consists of (1) a head-mounted display (HMD) (HTC Vive-VR); (2) a pair of wireless controllers; (3) two base stations, where steamVR® tracking technology tracks a subject’s exact location and movement through the headset and controllers; (4) a computer with a 4-core Intel® Core™ i5–4590 at 3.30 GHz, 8-GB random access memory (RAM), and a NVIDIA® Geforce® GTX 1070/MSI with 8 GB of GDDR5. Wearing the HMD and sitting in a wheelchair, subjects in the experimental group will interact with virtual objects in various scenarios.

**Fig. 3 Fig3:**
[figure not shown]
Virtual reality (VR) system and a virtual scenario. **a** A subject is wearing a VR system. **b** A subject is playing basketball

### VR training protocol

During the daily 30-min VR rehabilitation, subjects in the experimental group will be required to complete the six programs (kitchen, shooting gallery, playground, basketball court, boxing arena, fencing hall) shown and described in Fig. 4, playing different roles in a virtual environment. When using the HTC Vive-VR HMD, the patient can look around by physically turning the head to a limited degree.

**Fig. 4 Fig4:**
[figure not shown]
Six virtual reality (VR) programs. **a** Making scrambled eggs and frying dumplings in a virtual kitchen by controlling a hand and a pair of chopsticks, respectively. **b** Shooting ceramic plates and vases on a shelf by controlling a pistol in a virtual shooting gallery. **c** Playing a whack-a-mole game by controlling a wooden mallet hammer in a virtual playground. **d** Playing basketball in a virtual court, in which the ball is shot by a controller and the height and distance of the basket is varied over time. **e** Punching with dolls by controlling a big fist in a virtual boxing arena, in which the doll that is hit will retreat to its original position. **f** Popping balloons by controlling a sword in a virtual fencing hall

This is close to a realistic experience and provides a high level of immersion. In the early stages of rehabilitation, due to the poor function of the upper limb on the hemiplegic side, subjects will have to complete the VR programs with the help of the limb on the unaffected side. With the recovery of upper limb function on the hemiplegic side, the subjects will then independently complete the six games using the limb on the hemiplegic side.

### Primary outcome measure

The arm motor section of the Fugl-Meyer assessment (FMA) [32, 33], highly recommended as a clinical tool for evaluating changes in motor impairment after stroke [33], will be used to measure arm movement ability across several domains: motor function, balance, sensation, range of motion, and pain.

### Secondary outcome measures

We will apply MRI techniques to assess the performance of immersive VR-based rehabilitation and to investigate the brain mechanisms of rehabilitation, particularly in regions related to motor learning and motor control. Three different MRI modalities will be acquired: (1) high-resolution anatomical MRI (T1-MRI) for estimating anatomical parameters of cortex, subcortex, and structural connectivity; (2) resting-state functional MRI (RS-fMRI) for estimating the functional connectivity of brain regions; and (3) diffusion tensor imaging (DTI) for estimating tractographic parameters of white matter and the microstructure of gray matter. Each subject will be scanned three times (before rehabilitation, immediately following 3 weeks of rehabilitation, and 12 weeks post-rehabilitation). The brain parameters obtained by MRI will be assessed and correlation with the clinical outcome measures will be tested.

Other secondary outcome measures include: (1) Brunnstrom stage scores, which will be obtained for assessment of motor recovery of the upper extremities; (2) assessment of the subject’s’ mental state, which will be determined using the Hamilton Depression Scale (HAMD) [42] and the Hamilton Anxiety Scale (HAMA) [43]; (3) the activities of daily living (ADL), which will be determined using the Function Independent Measure (FIM) [44] and the Bathel Index (BI) [45]; (4) assessment of the severity of ischemic stroke and cognitive function, which will be determined using the National Institutes of Health Stroke Scale (NIHSS) [46] and the Korea-Mini Mental Status Evaluation (K-MMSE) [38], respectively. These stoke-associated measures will also be evaluated as covariates in regard to the primary outcome measure.

### Questionnaire data acquisition

All questionnaires will be collected on an electronic tablet on which the questionnaire software, Research Electronic Data Capture (REDCap), will be installed [47]. REDCap is a secure, convenient, and efficient online/offline Web application for capturing electronic survey data and is recommended by the National Institutes of Health for data collection in clinical trials.

### MRI data acquisition

Subjects will be scanned on a 3-T GE-Discovery 750 scanner at Wenzhou Medical University (WMU), China, equipped with the following: for anatomical T1-MRI data, repetition time (TR)TR/echo time (TE) = 7.7/3.4 ms, flip angle = 12°, field of view (FOV) = 256 mm × 256 mm, resolution = 256 × 256, slice per volume = 176, slice thickness = 1 mm; for RS-fMRI data, TE/TR = 30/2500 ms, voxel size = 3.4375 × 3.4375 × 3.5 mm^3^, in-plane resolution = 64 × 64, number of volumes = 230, and flip angle = 90°; and for DTI data, TR/TE = 8000/80 ms, flip angle = 90°, FOV = 256 mm × 256 mm, resolution = 128 × 128, slice thickness = 2 mm, slices per volume = 75, 23 volumes with b = 1000 s/mm^2^ and 49 volumes with b = 2000 s/mm^2^.

### MRI data processing

Data quality control: each imaging modality (T1, RS-fMRI and DTI) will undergo quality control and data with excessive motion or bad signal-to-noise ratio will be excluded [48]. Three different metrics are evaluated for each subject: (1) for T1, the volume of seven regions of interest (ROIs) and the stretch factor (transformation required to move the native-space in the brain to template space) is obtained; (2) for RS-fMRI, the temporal signal-to-noise ratio is calculated; and (3) for DTI, the mean fractional anisotrophy (FA) and mean diffusivity is obtained for specific ROIs and for white matter. These metrics must be met for the obtained scans to be accepted and to start the analysis for each modality.

The subjects’ structural T1 images will be analyzed using the FSL subcortical segmentation tool “FIRST” [49] and with the FSL gray matter density tool “VBM” [50]. From the results of FIRST, which includes 14 subcortical regions, and structural connectivity that correlates in 360 parcellations of cerebral cortex [51], we will find ROIs that may correlate with rehabilitation performance and continuing performance. Meanwhile, from the VBM result, the significant difference in local gray matter regions will be evaluated.

The subject’s RS-fMRI will be analyzed using FSL tools. First, we will use an independent component analysis (ICA)-based strategy for automatic removal of motion artifacts (AROMA) [52] to pre-process the data and correct resting images for motion. Second, we will regress out any signal found in ventricles and in white matter as these are considered artifacts. We will also remove the whole-brain global signal. To allow comparison between subjects, these filtered functional data will be registered to a standard brain and down-sampled to a 6 × 6 × 6 mm voxel size. A program produced in house called Apkarian Brain Linkage Mapping (ABLM), described and reported by Baria [53], will be used to provide the number of functional connectivity links of each brain voxel.

The subject’s DTI will be analyzed using FSL tools. We will use the diffusion toolbox “FDT” [54] to pre-process the DTI images. First, we will correct each subject’s DTI images for “eddy current” and then apply a “dtifit” algorithm to obtain a diffusion tensor model value at each white matter voxel. We will further extract the mean FA value of a group of voxels that may identify regions with significantly different white matter fiber microstructure [55, 56].

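### T1 and DTI scans must pass on regional volume, stretch factor, FA and diffusivity, which overlap with analysed MRI outcomes, so quality control could select scans on the result

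*Protocol article*

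**What the plan says.** The quality-control paragraph of MRI data processing has two layers.

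- **Technical exclusion.** For every modality, "data with excessive motion or bad signal-to-noise ratio will be excluded".
- **Metrics per modality.** "for T1, the volume of seven regions of interest (ROIs) and the stretch factor" are obtained; "for RS-fMRI, the temporal signal-to-noise ratio is calculated"; and "for DTI, the mean fractional anisotrophy (FA) and mean diffusivity is obtained for specific ROIs and for white matter". The paragraph closes: "These metrics must be met for the obtained scans to be accepted and to start the analysis for each modality".

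The same section then describes the analysis. For DTI: "We will further extract the mean FA value of a group of voxels", in order to identify regions where white matter microstructure differs. For T1, 14 subcortical regions from FIRST and structural connectivity are searched for regions that correlate with rehabilitation performance, and VBM is used to test local gray matter differences.

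The section Secondary outcome measures makes the MRI parameters secondary outcomes, taken at three visits and correlated with the clinical measures. It describes T1 as "high-resolution anatomical MRI (T1-MRI) for estimating anatomical parameters of cortex, subcortex, and structural connectivity".

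**The concern.** Motion and signal-to-noise describe how good an image is. Regional volume, FA and diffusivity describe the brain in the image, and the stretch factor depends partly on its anatomy. Every participant has an imaging-confirmed stroke, and the trial expects the brain to reorganise during follow-up. An unusual FA or regional volume may therefore be a true finding from a sound scan.

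If such a value is grounds for rejection, inclusion in the MRI analysis depends on the quantity being analysed. Two things follow. The range of the outcome is cut, which pulls arm differences and brain-behaviour correlations towards zero. And at weeks 3 and 15, if treatment moves the metric, the share of rejected scans differs by arm, so the scans compared are no longer a randomised comparison. The mechanistic half of the stated aim rests on these data.

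**Working it through.** **Step 1: is a gate metric also an outcome?**

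| Modality | Acceptance metric | Analysed quantity | Overlap |
|---|---|---|---|
| DTI | mean FA | mean FA of a group of voxels | same measure; same voxels not stated |
| DTI | mean diffusivity | not named; only under the general term for MRI brain parameters | only on a broad reading |
| T1 | volume of seven unnamed regions | FIRST (14 subcortical regions), VBM, connectivity | probable, not stated |
| T1 | stretch factor | none | registration quantity, though anatomy can move it |
| RS-fMRI | temporal signal-to-noise | functional connectivity links | none |

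The overlap is explicit for mean FA, probable for regional volume, and absent for RS-fMRI.

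**Step 2: the article's own power figure.** Inputs from Sample size considerations: two-sided 0.05, 80% power, 30 completers per group. Solving the two-sample t test for the detectable effect gives d = 0.736, which rounds to the stated 0.74; power at 0.74 is 80.5%. Recruitment is 60 / (1 − 0.25) = 80, as stated. These figures are sound and the point does not touch them. The 0.74 is borrowed below only as a convenient size of shift; the article does not assume it for FA.

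**Step 3: effect of gating on the outcome.** Assumptions: the gate metric is the outcome; control ~ N(0, 1), VR ~ N(0.74, 1); limits are k SD from the control mean. With μ the arm mean, L and U the limits, and φ and Φ the normal density and distribution function:

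- a = L − μ, b = U − μ
- share kept: K = Φ(b) − Φ(a)
- mean of kept scans: μ + [φ(a) − φ(b)] / K

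*Worked case, two-sided, k = 2.* VR: a = −2.74, b = 1.26, K = 0.893, mean = 0.74 + (0.0093 − 0.1804) / 0.893 = 0.549. Control mean stays at 0 by symmetry, with 95.4% kept. The observed difference is 0.55, a loss of 1 − 0.549/0.74 = 26%.

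*Worked case, lower limit only, k = 2.* Control mean = 0.055, VR mean = 0.749, difference 0.694, a loss of 6%.

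| k (SD) | Two-sided: difference | Loss | Kept, control v VR | Lower only: difference | Loss |
|---|---|---|---|---|---|
| 3 | 0.71 | 4% | 99.7% v 98.8% | 0.74 | under 1% |
| 2.5 | 0.65 | 12% | 98.8% v 96.0% | 0.72 | 2% |
| 2 | 0.55 | 26% | 95.4% v 89.3% | 0.69 | 6% |
| 1.5 | 0.39 | 47% | 86.6% v 76.4% | 0.63 | 14% |

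**Step 4: when gate and outcome are only partly related.** Simulation of 8,000 trials, 30 per arm, true difference 0.74 SD, lowest 10% of pooled gate values removed, then a t test:

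| Gate-outcome correlation | Observed difference | Power | Removed, control v VR |
|---|---|---|---|
| 1 | 0.55 SD | about 63% | 16% v 4% |
| 0.5 | 0.69 SD | about 73% | 13% v 7% |
| 0 | 0.74 SD | about 76% | 10% v 10% |

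The last row shows that removing 10% of scans unrelated to the outcome leaves the difference unbiased and lowers power only through smaller numbers. Bias appears only when the gate is related to the outcome.

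**The case against.** The best defence is that the paragraph has a technical purpose. It opens with motion and signal-to-noise, cites a quality-control reference, and may intend the listed metrics only as a way of catching gross acquisition or registration failure. The limits may be in that reference or in the full protocol, and their absence from an article is no fault. With wide limits the effect is slight: a lower limit at 3 SD leaves 0.74 SD intact to two decimals.

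Much of this stands. The missing cut-offs are not the complaint, and the size cannot be known without them. But the sentence makes meeting the metrics a condition of acceptance; it does not say they trigger a second look. Supplying numerical limits elsewhere would not change what is being gated on.

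A reader might infer several stronger things that the article does not support:

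- *That quality control does select patients on the result.* No limit or direction is given, so this is a risk and not a demonstrated fact. Acceptance is by modality, so a rejected DTI scan need not remove the patient from other analyses.
- *That the most damaged patients are removed.* This needs a lower cut, which is nowhere stated.
- *That every gated metric is an outcome.* Diffusivity is not named as one, the stretch factor is not one, and the seven regions are unidentified.
- *That power falls to about 63%.* That figure needs the gate and the outcome to be identical and a tenth of scans to be cut from one tail, which is near the worst case.
- *That rejected follow-up scans would be filled by carrying the baseline forward.* The missing-data rule in Statistical analysis does not say whether it covers MRI.

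**Conclusion.** The point holds as a fault in a stated rule, limited to the secondary MRI outcomes from T1 and DTI. Acceptance depends on brain measures, one of which (mean FA) is also analysed and another of which (regional volume) probably is. In a stroke population that could select scans on the result, differently by arm at post-randomisation visits, and attenuate arm differences and brain-behaviour correlations.

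The size is unknown. Under the assumptions that the gate is the outcome, values are normal and the true shift is 0.74 SD, the loss runs from about 4% to 47% for two-sided limits at 3 to 1.5 SD, and from under 1% to 14% for lower limits alone. It shrinks further when gate and outcome are only partly correlated. RS-fMRI, gated on temporal signal-to-noise, and the primary outcome, the arm section of the Fugl-Meyer assessment, are not affected.

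**What to change.** Reword the quality-control paragraph so that:

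- T1 and DTI scans are rejected only for technical failure (motion, signal-to-noise, acquisition or registration failure), judged blind to arm;
- regional volume, stretch factor, mean FA and mean diffusivity serve only to flag a scan for that re-inspection and are not themselves grounds for rejection;
- the number of rejected scans is reported by arm and visit, with the technical reason.

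The RS-fMRI rule can stay. The cost is a change of wording and a short blinded re-check of flagged scans. The downside is that a few noisy scans may be kept.
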